#### Qualitative outcomes

A subset of participants randomised to TPI+TAU will be invited to take part in an optional 30-minute telephone or videocall interview to explore their experiences of the TPI.

Online supplementary material 5 outlines the completion time points for each measure.

### Adherence measures

Adherence is defined as the extent to which participants engage with the prescribed components of the TPI, including attendance at the TPS, and ongoing participation in psychological therapy. This will be assessed through dropout rates and TPS and session attendance over the course of therapy.

As is normal practice within the host clinical service, participants will be asked to refrain from receiving any talking therapy outside of that provided within the trial for the duration of their participation. This adherence will be verified during the screening phase and reinforced during the agreement stage of their therapy with the host service.

### Safety outcome measures

Data on the impact of the intervention on reducing depression and other outcome measures will not be analysed until the end of the study period and therefore will not inform decisions to stop the research. If participant responses or communications raise concern about safety (eg, deterioration or risk), the research team will follow predefined escalation procedures, including liaison with the participant’s clinical team and signposting to urgent support in line with NHS care pathways.

Adverse events (AEs) are any medical or psychological events experienced by a participant during a study, regardless of whether they are caused by or related to the intervention being tested, and requiring documentation and independent oversight to ensure participant safety, while SAEs have significant outcomes such as death or hospitalisation. Participants may report AEs directly to researchers, during assessments, or via clinicians. Any AEs will be assessed for seriousness and causality by the CI, recorded and monitored until resolution. SAEs will be reported to the CI and study sponsor within 24 hours, and their relevance to the intervention will be determined with clinical input. Participants may be withdrawn at the CI’s discretion if necessary.

All SAEs will be reviewed by the CI and study sponsor and, if there is any indication that these are linked to the intervention, consideration will be given to stopping on the advice of the TSC, the National Institute for Health Research Applied Research Collaboration East Midlands (NIHR ARC-EM) Scientific Committee and study sponsor. For quality assurance, the sponsor, ethics committee or an independent study monitor may audit trial conduct through site visits. During such visits, direct access to source data and trial documentation will be granted, with all parties maintaining strict confidentiality of participant data.

### Data collection and management

Data will be collected and managed using REDCap. Each participant will be assigned a unique trial identification number to maintain confidentiality; identifying information will be stored separately from outcome data. Online assessments will be completed by participants, while phone assessments will be entered by researchers. Only researchers in contact with participants and the EMCA CPH administrative team will access identifiable data. All data will be stored securely and handled in compliance with data protection regulations, sponsor policies and ethical standards.

Participants will complete a baseline assessment and follow-ups at weeks 4, 8, 12 and 24 post randomisation. Surveys should be completed within 7 days of the due date. REDCap will send automated emails 1 week prior, with reminders 4 days after the due date if incomplete. Assessments not completed within 7 days will be marked as missed but not considered a withdrawal unless formally notified. Participants missing the final assessment without contact will be classified as lost to follow-up.

### Statistical methods

More information about the statistical methods can be found in the statistical analysis plan (SAP), in online supplementary material 6.

#### Sample size calculation

Based on the established Minimally Clinically Important Difference on the PHQ-9 (~3 points or ~20% of baseline severity^39^) and consistent with previous trials in cancer patients,^40^ 90 participants are needed to detect a 3-point difference with 90% power at α=0.05. This is based on prior service data: SD=5.5, baseline–follow-up correlation=0.30 and correlation among follow-ups=0.63. To account for unequal centre recruitment and clustering, a design effect of 1.336 was applied. Factoring in a 20% attrition rate, the final required sample size is 150. Power analysis was conducted using Stata 18 (StataCorp LLC, USA).

#### Statistical methods for primary and secondary outcomes

De-identified datasets will be downloaded from REDCap for analysis, which will follow an intention-to-treat (ITT) approach. Exploratory analyses of primary and secondary outcomes will precede formal analysis. Multilevel modelling will estimate treatment effects and their precision over follow-up, using participants as level 2 units, with baseline measures, minimisation factors, allocation, follow-up time and follow-up×allocation interaction as fixed-effect covariates.

The final SAP will detail planned ITT and sensitivity analyses for all outcomes. All trial data will be stored and analysed on secure University of Nottingham platforms using the latest version of Stata.

Missing outcome data will be assessed and reported by treatment group and timepoint. Multiple Imputation, assuming a Missing At Random (MAR) mechanism, will be used to address missing data. Sensitivity analyses will test the robustness of treatment effects against assumptions, limitations and analytical methods.

No interim analyses are planned.

#### Methods for additional analyses (eg, subgroup analyses)

### Qualitative analysis

A subsample of 20 participants, randomised to TPI+TAU and consenting to optional interviews, will be selected based on availability. These interviews will explore participants’ experiences of the TPI, its perceived impact and effects. If thematic saturation is not reached after 20 interviews, additional interviews will be conducted.

Semi-structured interviews will take place via telephone or Microsoft Teams after final follow-up. Anonymised transcripts will undergo Reflexive Thematic Analysis using Braun and Clarke’s six-step approach.^42^

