## Introduction

### Background and rationale

 The prevalence of common mental health problems among people diagnosed with and treated for cancer is up to four times higher than that observed in the general population,^1^ leading to an elevated risk of suicide and diminished quality of life lasting for more than 10 years after diagnosis.^2 3^ These difficulties often go untreated, which has multiple deleterious effects including negative impacts on the patients’ concordance with cancer treatment.^4 5^ Evidence-based psychological therapies, such as cognitive behavioural therapy (CBT), are shown to be effective in improving mental health outcomes for people living with and beyond cancer.^6^ However, timely access to these interventions is a key challenge. Patients referred for psychological therapies typically wait several weeks or months before gaining access to treatment^7^ and the longer patients wait, the greater the risk of their mental health worsening.^8^,^12^

Patients’ engagement with treatment can also be affected by long waits. For example, only 55% of people accessing UK National Health Service (NHS) Talking Therapies for anxiety and depression attend more than one session.^13^ For people living with and beyond cancer, therapy engagement can be even more challenging due to the multiple competing demands of managing their physical health, treatment side effects and cancer-related stressors.^14^ Moreover, the likelihood of dropout increases when patients experience long wait times without any input,^15^ highlighting the need for interventions that support engagement from the point of referral. Besides dropout rates, there are wider engagement challenges in ensuring that patients fully use therapy to achieve the greatest benefits, such as potential ambivalence about change.^16^

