### Hypothesis

We hypothesise that participants receiving the therapy preparation intervention (TPI) plus treatment as usual (TAU) will show greater reductions in depression symptoms, lower dropout from psychological therapy and improved secondary outcomes including anxiety, functioning, mental well-being, patient activation, readiness for change and health-related quality of life compared with those receiving TAU alone. Additionally, we expect TPI participants to demonstrate greater improvement in hope and in session indicators of activation and engagement.

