## Methods and analysis

### Study design

The PROSPER study is a two-arm, multicentre, parallel-group, single-blind randomised controlled trial comparing TPI+TAU versus TAU alone over 24 weeks for moderate-to-severe depression in current or former cancer care patients in the East Midlands region of England. Participants will be recruited from existing psychological therapy referral pathways across primary and secondary NHS cancer care services, including secondary care cancer centres and primary care general practices. All participants will provide informed consent prior to being randomised. Patient flow and study procedures are shown in figure 1. The study is overseen by an independent Trial Steering Committee (TSC), with the same group acting as a Data Monitoring Committee (DMC). The trial will be reviewed every 6 months through reports to this committee and presentations of progress to the committee by the study team. Participants in both arms will receive the same outcome measures. Follow-ups will occur at 4, 8, 12 and 24 weeks post randomisation. A nested semistructured interview study will explore participants’ experiences with TPI+TAU. Interviews will be conducted no earlier than 2 weeks after the 24-week follow-up assessment is due.

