#### Primary outcomes

The primary outcome is change on the PHQ-9^37^ score across 4-week, 8-week, 12-week and 24-week follow-ups. Follow-up dates will be calculated from the date of randomisation.

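### Choosing TPI interviewees by availability, at least 26 weeks after randomisation and with no stated spread by engagement, risks under-representing those who disengaged

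*Protocol article*

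**What the plan says.** The protocol article states a selection rule for the nested interviews. Under Qualitative analysis, 20 participants "randomised to TPI+TAU and consenting to optional interviews, will be selected based on availability". The number may grow: "If thematic saturation is not reached after 20 interviews, additional interviews will be conducted". Qualitative outcomes confirms that the interview is voluntary and confined to one arm: "A subset of participants randomised to TPI+TAU will be invited to take part in an optional 30-minute telephone or videocall interview".

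On timing, Study design says: "Interviews will be conducted no earlier than 2 weeks after the 24-week follow-up assessment is due". Primary outcomes sets the clock: "Follow-up dates will be calculated from the date of randomisation".

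On purpose, Qualitative analysis says: "These interviews will explore participants’ experiences of the TPI, its perceived impact and effects". The Hypothesis section expects "lower dropout from psychological therapy and improved secondary outcomes" with the TPI, and Engagement outcomes compares attendance and dropout between arms.

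**The concern.** The TPI is meant to keep people in therapy, so the experience of those it did not keep is informative about its perceived impact. The sample passes two filters, consent to an optional interview and availability about half a year after randomisation. Neither is balanced by any stated criterion on engagement.

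The Background section gives reason to think that the filters are not neutral. It says that engagement is harder in cancer because of competing physical health demands, side effects and stressors. The same pressures could plausibly make a person unavailable for an interview. The saturation rule does not protect against this: themes can saturate among the people interviewed without showing who is absent.

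At stake is the balance of the qualitative findings. The article's list of strengths presents the mixed-methods design as a route to a fuller understanding of outcomes and mechanisms, and its limitations do not mention interview selection. A sample weighted towards engaged participants could make the TPI look more acceptable than it was across the arm.

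**Working it through.** **Timing.** The 24-week assessment is counted from randomisation, and interviews start at least 2 weeks after it is due: 24 + 2 = 26 weeks.

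**Pool.** 160 participants were recruited (Trial registry and status) with 1:1 allocation (Randomisation and blinding), so the TPI+TAU arm holds about 160 / 2 = 80. Twenty interviews are about 20 / 80 = 25% of it, which leaves room for a sampling frame.

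**Who may be interviewed.** Three passages bear on whether disengaged participants are shut out:
- Qualitative analysis: eligibility rests on allocation, consent and availability, not on completing therapy.
- Study design: the interview date runs from when the assessment is due, not from its completion.
- Data collection and management: a missed survey is not a withdrawal unless formally notified.

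So dropouts remain eligible. The question is only how many would be reached.

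**Illustration of size.** Let *q* be the share of the arm that is disengaged and *r* their availability relative to the rest. The documents give neither, so both are assumptions. The expected share among interviewees is

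s = q·r / (q·r + 1 − q),

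the expected number is 20·s, and the chance of no disengaged interviewee is about (1 − s)^20 (binomial approximation).

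| q | r | s | Expected of 20 | Chance of none |
|---|---|---|---|---|
| 0.20 | 1.00 | 0.200 | 4.0 | 1% |
| 0.20 | 0.50 | 0.10/0.90 = 0.111 | 2.2 | 10% |
| 0.20 | 0.25 | 0.05/0.85 = 0.059 | 1.2 | 30% |
| 0.30 | 1.00 | 0.300 | 6.0 | 0.1% |
| 0.30 | 0.50 | 0.15/0.85 = 0.176 | 3.5 | 2% |
| 0.30 | 0.25 | 0.075/0.775 = 0.097 | 1.9 | 13% |

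The value 0.20 is borrowed from the attrition allowance in the sample size section, which is loss to the trial and not dropout from therapy; 0.30 is a plain assumption. Across these inputs about 1–4 of 20 interviewees are disengaged, against 4–6 if they were as available as everyone else. The direction holds whenever r is below 1. The size depends on the assumed inputs.

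**The case against.** Several counter-arguments have weight.

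- **Dropouts are not excluded.** A reader might infer that the rule leaves them out. The three passages compared above show that it does not, and the illustration itself expects some among 20. Only under-representation is supported.
- **Nothing shows that the sample would be well.** A reader might infer selection of people who improved. The documents do not link availability to recovery, and improved patients discharged from the service could also be hard to reach.
- **A null result on dropout.** A reader might infer that this sampling would leave such a result unexplained. About 20 interviews in one arm could not alone explain a between-arm null however they were chosen, and the stated aim is experience of the TPI, not reasons for leaving therapy. Dropout itself is compared from attendance records.
- **The cited attendance figure.** The Background says that "only 55% of people accessing UK National Health Service (NHS) Talking Therapies for anxiety and depression attend more than one session", and a reader might take the 45% complement as this arm's disengagement rate. It describes general services, not this one, and attending one session or none is not the same as dropping out of this therapy. It cannot size the problem here.
- **The timing has a purpose.** Late interviews keep an extra contact, given to one arm only, out of the PHQ-9 follow-up period. This stands, and the timing need not change.
- **Condensed reporting.** Fuller qualitative methods may lie in documents not shown. That would answer a missing detail, but the article names a criterion, and the criterion is availability.

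What survives is that the stated rule does nothing to secure a spread by engagement.

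**Conclusion.** The point holds as a risk of under-representation in the nested qualitative study. Followed as written, the rule tends to yield fewer disengaged TPI participants than the arm contains, provided that they are less available than others. That premise is plausible from the protocol's own rationale but is not measured in it. Under the assumed inputs the shortfall is roughly 1–4 interviewees instead of 4–6, and this is an illustration, not an estimate for this trial. The consequence is that the account of the TPI could be too favourable. The randomised comparison, sample size, primary and secondary analyses and economic evaluation are unaffected.

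**What to change.** Replace the availability rule under Qualitative analysis with purposive, maximum-variation selection from consenting TPI+TAU participants. Use two criteria: attendance at the preparation session, and therapy status (not started, dropped out, completed). Both come from attendance data that Engagement outcomes and Adherence measures already require. The trial manager, who is unblinded under Randomisation and blinding, can apply the frame. Seek a stated minimum number from the disengaged groups before judging saturation. In the report, set interviewees' attendance and dropout status beside those of the whole TPI arm.

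Do not sample on PHQ-9 change while follow-up continues. The first participant was recruited on 29 October 2024, so interviews could begin about 26 weeks later, in late April 2025. Recruitment closed on 14 August 2025, so 24-week assessments run to about the end of January 2026. In between, choosing on PHQ-9 change would sit badly with the blinding of assessors and analysts and with the statement under Safety outcome measures that outcome data are not analysed until the end of the study.

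The costs are slower filling of the interview places and a minor amendment, since Ethics and dissemination sends all protocol amendments to the ethics committee and has the sponsor and funder notified. If interviews have already begun, apply the frame to those remaining or to the additional ones that the protocol allows. The comparison with the whole arm can be reported in any case.

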### Economic evaluation

A within-trial economic evaluation will be conducted to assess cost-effectiveness from both health/social care and broader societal perspectives; full methods are detailed in online supplementary material 5.

### Oversight and monitoring

The CI has overall responsibility for the study and data custody, supported by the research team. The coordinating site, staffed by the University of Nottingham, manages trial operations. The Trial Management Group (comprising the CI, study researchers, trial manager and statistician) will meet fortnightly to monitor progress and address issues.

An independent NIHR ARC-EM Scientific Committee, external to the research team’s institutions, will review trial progress every 6 months. The study team will also meet with Patient and Public Involvement and Engagement (PPIE) members every 6 weeks to review recruitment and participant engagement.

The TSC/DMC, comprising a statistician, practitioner psychologist and PPIE representative, will provide independent oversight of the trial. Meeting at least every 6 months, the TSC/DMC will monitor trial conduct, participant safety, recruitment progress and data integrity, and will review recruitment and measure completion 6 months after initiation to assess feasibility. The committee will also review all reported AEs, which will be assessed for seriousness, expectedness and causality, and documented in participants’ records and case report forms (CRFs).

### Ethics and dissemination

Ethical approval for this trial was granted by the London - Bromley Research Ethics Committee (REC reference: 24/LO/0610) on 26 September 2024. The study will be conducted in accordance with Good Clinical Practice and the Declaration of Helsinki. All participants will provide informed consent before taking part.

Following participation, individuals can continue to access support for depression through their usual care pathways. Once discharged from EMCA CPH, participants will only be able to return to the service if formally re-referred by their clinical team and meeting the service’s standard eligibility criteria.

Dissemination will include sharing findings with participants who have consented to receive study results. In addition, results will be presented at national and international conferences, alongside publication in peer-reviewed journals. This document constitutes the full trial protocol. Requests for participant-level data or access to statistical code should be directed to the corresponding author. All protocol amendments will be submitted to the relevant ethics committee for approval. The sponsor and funder will also be notified, and the CI will ensure all study sites receive updated protocols for their Investigator Site Files. Any deviations will be documented using a breach report form, and the trial registry (https://www.isrctn.com/ISRCTN13692666) will be updated accordingly.

### Trial registry and status

The trial actively recruited via primary and secondary care NHS sites. Recruitment opened on 17 October 2024, and the first participant was recruited on 29 October 2024. Recruitment closed on 14 August 2025, by which time 160 participants had been recruited, exceeding the planned sample size of 150.

The trial was registered on ISRCTN on 18 October 2024: 13692666.

### Significance

The PROSPER trial addresses a critical and under-researched gap in psychological care for patients living with and beyond cancer who are experiencing depression while awaiting therapy, a period often marked by deterioration in mental health and leading to reduced engagement with services. This study evaluates the effectiveness of a brief, preparatory psychological intervention enhanced with personalised smart messaging, aiming to improve therapy readiness, adherence and clinical outcomes.

If found to be effective, the TPI could make a significant contribution to the evidence base supporting brief pre-treatment interventions for individuals awaiting psychological therapy. It would strengthen the rationale for incorporating such interventions into cancer care pathways. The integration of smart messaging represents an important innovation, with evidence that digital messaging can reinforce behavioural change, sustain motivation and increase patient activation, offering a low-cost, scalable adjunct to in-person care.^31 34^

From a clinical and health systems perspective, the findings of the PROSPER trial may inform future models of care delivery, particularly in oncology and other settings where there are delays in accessing behaviour change interventions. If the intervention is shown to be cost-effective and feasible to deliver by a range of trained staff, it could support service efficiency by reducing dropout rates and improving therapy outcomes. The pragmatic design of the trial, embedded within routine NHS care pathways, enhances the real-world relevance of the findings and supports the potential for widespread implementation.

